The proposed study will be conducted in Vietnam, which has among the highest prevalence levels of human STH of any Western Pacific country [20]. Diarrheal disease also remains a major cause of mortality and morbidity in children in Vietnam, with 11 % of deaths in children aged 0–5 years being due to diarrhea [21]. Recently, the causative agents of diarrheal disease in children under 5 years of age in Ho Chi Minh City, Vietnam, were identified, with Norovirus, Rotavirus, *Campylobacter, Salmonella,* and *Shigella* being the main pathogens isolated from diarrheal patients [22]. Further analysis of a subset of these samples by real-time polymerase chain reaction (PCR) found STH eggs in 6/342 (1.8 %) diarrheal samples, whereas 41/123 (33.3 %) of healthy control samples were positive for STH (our unpublished data). Previous studies have found that real-time PCR is sensitive enough to detect even one STH egg in 200 mg of fecal material [23]. No statistical differences in demographics or personal hygiene between helminth-infected and helminth-uninfected individuals were present, including age, sex, address, household size and income, water and food resources, toilet type, probiotic usage, or hand-washing practice. The significantly higher prevalence of STH infections in healthy controls compared to diarrheal patients suggests that STH may be beneficial to children in combating the pathogens that cause diarrhea. Thus, the primary objective of this study is to investigate the effects of 400 mg albendazole treatment on the incidence of diarrheal disease caused by viral and bacterial pathogens in school children in southern Vietnam. This study will provide new insights into the role of co-infections in the success of treatment strategies and may inform public health policies to mitigate indirect effects of mass deworming programs.

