#### Clinical trial

From the baseline study, 350 helminth-infected and 350 helminth-uninfected children will be enrolled in the subsequent clinical trial. These consented participants will complete a short questionnaire regarding changes to their contact information, and a study nurse will measure their height and weight. Albendazole or placebo treatment will be administered once every 3 months for 12 months. At the 12-month time point, all participants will receive albendazole treatment. Stool samples will be collected once every 3 months (immediately before any treatment is administered) and 2 weeks after the first and third treatments to evaluate the efficacy of anthelmintic treatment in helminth removal and to quantify variation among individuals in their propensity to acquire helminth infections. Parents/guardians will be contacted weekly by phone to request information on whether their child has experienced any diarrheal episodes in the preceding 7 days. When a participant alerts the study nurse of a diarrheal episode, the study nurse will travel to the individual’s home to collect a stool sample and to administer a short questionnaire regarding the participant’s diarrheal symptoms and duration. A sterile stool collection pot will also be left with the parents/guardians for a stool sample collection 2 weeks after the last diarrheal episode. Four milliliters of venous blood will also be collected by the study nurse once every 6 months to measure hematocrit levels and any changes to immunity with helminth infection and removal over time. A finger-prick blood sample will also be collected in the third and the ninth month of the study to measure hematocrit levels in all children (Fig. 1).

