#### Secondary endpoints

The secondary endpoints are:Prevalence and intensity of soil-transmitted helminth infections at 0, 0.5, 3, 6, 6.5, 9, and 12 months, and during and 2 weeks after cases of diarrheaPrevalence and intensity of enteric viral and bacterial infections that cause diarrhea at 0, 3, 6, 9, and 12 months, and during and 2 weeks after cases of diarrheaChanges in fecal microbiota composition at 0, 0.5, 3, 6, 9, and 12 months, and during and 2 weeks after cases of diarrheaChanges in blood cytokine levels (TH1, TH2, TH17, and Treg) at 0, 6, and 12 monthsAntibody isotype responses to helminth and diarrheal antigens at 0, 6, and 12 monthsMean *z* scores (height-for-age, weight-for-age, weight-for-height) at 0 and 12 monthsNumber and severity of adverse events (AE) during the 12-month study period

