
### Statistical analysis

The main analysis population includes all randomized participants, and the analysis will be conducted according to the randomized treatment arm following the intention-to-treat principle. Subgroup analyses according to helminth infection status at enrollment (infected versus uninfected) will also be performed for all endpoints.

The primary endpoint, the number of diarrheal episodes per subject, will be compared between the two study arms based on mixed-effects Poisson regression models, with treatment as the main covariate and adjustment for helminth infection status at enrollment (infected versus uninfected). To account for subjects lost to follow-up, the subject’s (log-transformed) follow-up duration will be included as an offset in the Poisson regression model. Moreover, to account for potential heterogeneity (i.e., larger between-participant variability than expected by the Poisson regression model), the participant variable will be included as a random effect in the model. If necessary, a random effect of family or household will also be included to account for non-independence of siblings or other co-inhabitants of a household. In a second step, the effect of the following covariates on diarrheal incidence will be explored: age, sex, body mass index, and household characteristics (e.g., type of water supply). A random effect of individual will be included to account for non-independence of repeated diarrheal episodes for a given individual. Additionally, the effect of helminth infection and helminth infection intensity, as determined from longitudinal stool samples, on diarrheal incidence will be investigated.

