For the secondary endpoints, the proportion of participants with STH and enteric viral and bacterial infections, as well as the infection intensities at each time point, will be summarized and visualized as line-plots over time. Formal comparisons between the treatment arms will be based on logistic mixed-effects models for proportions and linear mixed-effects models for (log-transformed) intensities using the same covariates and random effects as for the primary endpoint. The baseline measurements will be included in the analysis, but modeled as not depending on treatment arm. For the main comparison between treatment arms, only stool samples from scheduled visits will be included, as stool samples collected 2 weeks after diarrheal episodes may be unequally distributed between treatment arms. However, these additional stool samples will be included in the exploratory analyses. The effect of additional household and environmental factors present at baseline on helminth, viral, and bacterial infections will also be investigated using the same statistical modeling approach outlined above.

The taxonomic composition of the gut microbiota will be analyzed before and after helminth infection, anthelmintic treatment, and diarrhea and will be compared with individual baseline levels, between the two treatment arms, and between helminth-infected and helminth-uninfected individuals. The mothur pipeline [37] will be used to detect microbial composition and diversity between and within samples based upon the proportion of OTUs in each sample and to apply appropriate corrections for any differences driven by rare taxonomic groups of microbes. Tests, such as the LDA Effect Size (LEfSe) algorithm [38], will be used to identify significant differences in bacterial taxa between the different groups of interest.

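### The exploratory analysis of helminth infection and diarrhea does not keep diarrhea-triggered stools out of the exposure, so exposure measurement can depend on the outcome

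*Protocol article*

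**What the plan says.** All references are to the protocol article.

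- **Statistical analysis, after the primary model and the covariate step:** "the effect of helminth infection and helminth infection intensity, as determined from longitudinal stool samples, on diarrheal incidence will be investigated". No restriction to scheduled stools is given, and none to stools taken before the episodes being counted.
- **Statistical analysis, secondary endpoints:** "For the main comparison between treatment arms, only stool samples from scheduled visits will be included". The reason given is that "stool samples collected 2 weeks after diarrheal episodes may be unequally distributed between treatment arms". The text then adds that "these additional stool samples will be included in the exploratory analyses".
- **Clinical trial (follow-up and sample collection):** at each reported episode the nurse visits the "home to collect a stool sample and to administer a short questionnaire", and a pot is left "for a stool sample collection 2 weeks after the last diarrheal episode". Each episode can therefore add two stools.
- **Secondary endpoints:** "Prevalence and intensity of soil-transmitted helminth infections at 0, 0.5, 3, 6, 6.5, 9, and 12 months", plus measurements during and 2 weeks after diarrhea. That makes 7 scheduled helminth measurements.
- **Parasite detection in stool samples:** real-time PCR for helminths is run on every stool collected, so triggered stools do yield a helminth result.

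**The concern.** In a model of helminth status on number of episodes, the outcome is the episode count. If triggered stools feed the exposure, the number and timing of exposure measurements are set by that same count. A child with many episodes is tested more often, and the extra tests come at or after the event. An association can then appear in either direction without any helminth effect.

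The article recognizes that these stools depend on diarrhea and protects the arm comparison from them. It gives no similar protection to the analysis where the dependence is most direct. That analysis bears on the trial's motivating idea that helminths may protect against diarrhea, and the Discussion hopes to inform public health policy.

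**Working it through.** The plan attaches no figure to this analysis, so there is none to reproduce; the sample-size calculation is not involved.

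**Inputs from the article.** 7 scheduled helminth measurements; up to 2 triggered stools per episode; 700 children, 350 per helminth stratum; probability 0.6 of at least one episode in a year. Under a Poisson count this gives a mean of −ln(1 − 0.6) = 0.916 episodes per year.

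**Assumptions.** Per-stool positivity, between-child variation in episode rate (gamma frailty) and relative detection in triggered stools. The article gives none of these for this population.

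**Mechanism by hand.** With k episodes a child has 7 + 2k stools: 7 if k = 0, 13 if k = 3. Take the same per-stool positivity p = 0.10 in both children.

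- Ever positive = 1 − (1 − p)^n. For k = 0: 1 − 0.9^7 = 0.52. For k = 3: 1 − 0.9^13 = 0.75. If only the 2-week stool is added (n = 10): 1 − 0.9^10 = 0.65.
- Expected proportion positive, equal detection: 0.10 for both children.
- Expected proportion positive, detection halved in both triggered stools: for k = 3, (7 × 0.10 + 6 × 0.05)/13 = 1.00/13 = 0.077, against 0.10 for k = 0.

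So ever positive is pushed toward a harmful association. Proportion positive is pushed toward a protective one, but only if detection is lower.

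**Null simulations (no true helminth effect, 700 children, mean 0.916).** Rate ratios compare ever with never positive, or all with no stools positive.

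*A.* 300 runs per setting, unadjusted; positivity 0.2 to 0.5 in infected and 0.05 to 0.10 in uninfected children; frailty variance 1 or none; two triggered stools per episode, with any reduction in detection applied only to the stool taken during the episode.

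| Exposure | Rate ratio | False positives (nominal 5%) |
|---|---|---|
| Scheduled stools only, either coding | 0.96 to 1.02 | 2% to 7% |
| Ever positive, all stools, equal detection | 1.16 to 1.82 | 42% to nearly 100% |
| Ever positive, all stools, detection halved | 1.12 to 1.62 | 26% to 98% |
| Proportion positive, all stools, equal detection | 0.96 to 1.02 | 3% to 7% |
| Proportion positive, all stools, detection halved | 0.53 to 0.83 | 17% to 38% |

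*B.* Mean positivity 0.24, frailty variance 0.5. Two triggered stools: ever positive 1.24 (52% false positives), proportion positive with halved detection 0.59 (69%). One triggered stool: 1.14 (27%) and 0.72 (33%). Scheduled only: 0.98 to 1.00 (4% to 5%).

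*C.* 350/350 strata, adjusted for arm and stratum, one or two triggered stools. Ever positive 1.14 to 1.49; proportion positive with halved detection 0.38 to 0.57; proportion positive with equal detection 0.98 to 0.99; scheduled only about 1.0.

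C is closest to the trial's design and model. B and C also cover one triggered stool per episode, the narrower reading of the text. Together they give the summary ranges of about 1.1 to 1.5 and 0.4 to 0.7. A shows that other assumptions move these limits. None of the three is offered as a forecast.

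**The case against.** **Inclusion is inferred.** A reader might conclude that the plan expressly builds exposure from triggered stools. It does not. The sentence on exposure names no triggered stools. The sentence readmitting them stands under the secondary endpoints, where infection is the outcome, and may mean exploratory analyses of those endpoints only. Its wording also refers to the 2-week stools, not those taken during an episode. This stands, and limits the claim to what the text allows. Still, it is the article's only rule on these stools outside the arm comparison, and it points to inclusion. The problem persists, smaller, with the 2-week stool alone.

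**Coding belongs in the analysis plan.** Neither ever positive nor proportion positive appears in the article. Proportion positive with equal detection shows no bias, and exposure taken strictly before each episode would avoid it. The individual random effect is compatible with time-varying records. This also stands as to coding, and missing detail is not the complaint. The complaint is that the article makes a positive statement about using these stools without excepting the analysis they would distort.

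**The pilot figures.** It is tempting to read the Background figures, 6/342 (1.8%) STH-positive in diarrheal samples against 41/123 (33.3%) where "healthy control samples were positive for STH", as showing that diarrheal stool hides helminths. They do not. They compare different children, and cannot separate a biological difference from lower detection. Halved detection is purely an assumption, and is less natural for a stool taken 2 weeks after the episode.

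**Scope.** A reader might fear for the main result. The randomized primary comparison uses arm, not stool results, and the main between-arm helminth comparison already excludes triggered stools.

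**Conclusion.** The concern holds as a gap in an exploratory, non-randomized analysis. As written, the two statements together permit exposure measurements whose number and timing depend on the outcome. With no true effect, the resulting rate ratio could be about 1.1 to 1.5 for ever positive, or about 0.4 to 0.7 for proportion positive if detection in triggered stools is halved. With equal detection, proportion positive is unbiased; with scheduled stools only, the result is about 1.0. Size and direction rest on an exposure coding the article does not state and on assumed positivity, frailty and detection. The simulations also model no clearance of infection by albendazole. This is a minor-to-moderate improvement, and the main results do not depend on it.

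**What to change.** In the Statistical analysis section, state that exposure in this analysis comes only from scheduled stools preceding the period at risk. One workable form:

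- Split follow-up at the 3-monthly visits. Take infection status and intensity from the scheduled stool opening each interval (months 0, 3, 6 and 9).
- Count episodes in that interval, with its log person-time as offset.
- Adjust for arm and baseline helminth stratum, and keep the participant random effect.
- Exclude diarrhea-triggered stools from exposure, except in a labelled sensitivity analysis.
- Report the result as observational.

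One point to settle when writing this: the opening stool is taken just before the dose, so in the albendazole arm status may change soon afterwards. Results by arm, or a further split at the scheduled 0.5- and 6.5-month stools, would show whether this matters.

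The cost is a few sentences and the interval-split programming, with no new data. The small downside is that infections seen only in triggered stools are not used as exposure.

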### Study area

This study will be conducted in three primary schools in Cu Chi district in Ho Chi Minh City, Vietnam. Cu Chi is a peri-urban district on the northwestern border of Ho Chi Minh City. The climate of Cu Chi district is temperate with two distinct seasons: a rainy season from May to November and a dry season from December to April. Agriculture is the main source of income in the province. In 2010, Cu Chi district had a population of approximately 355,822 people, with a population density of 819 persons/km^2^ [24]. A prior study indicated that hookworm infections are the predominant STH in this area, with most children experiencing low infection intensities [25]. Although parts of Vietnam participate in the national deworming program administered by the WHO, the primary schools involved in this study have not provided deworming medication to their school children since January 2014 due to financial costs of the medication. The schools have no plans to provide anthelmintic medication to school children in the upcoming year.

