Cytokine levels and antibody profiles in response to parasite-specific antigens will be analyzed from longitudinally collected blood samples. Cytokine and antibody data will be log-transformed for all analyses, and linear mixed-effects modeling for analysis will be conducted as outline above. Additionally, changes in height-for-age, weight-for-age, and weight-for-height *z* scores between baseline and 12 months will be compared between the two treatment arms based on linear regression with adjustment for the baseline *z* score. Random effects to account for non-independence of siblings or other co-inhabitants from the same household will be included if necessary. Additionally, the overall number of participants with at least one adverse event (AE) or serious adverse event (SAE), respectively, will be compared between the two study arms using Fisher’s exact test. Descriptive tables will be used to summarize the frequency of all recorded AEs and SAEs by arm.

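### The stated covariates for the repeated-measures secondary models omit visit while baseline is kept as an arm-independent response, so taken literally much of any change common to both arms is attributed to albendazole

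*Protocol article*

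**What the plan says.** All references are to the Protocol article.

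- **Primary model** (Statistical analysis). The number of episodes per child is modelled "with treatment as the main covariate and adjustment for helminth infection status at enrollment (infected versus uninfected"), and "the participant variable will be included as a random effect in the model". A household effect is added if needed. Each child contributes one count, so no time term is required.
- **Infection endpoints** (Statistical analysis). The formal between-arm comparisons use logistic mixed models for proportions and "linear mixed-effects models for (log-transformed) intensities using the same covariates and random effects as for the primary endpoint". The next sentence reads: "The baseline measurements will be included in the analysis, but modeled as not depending on treatment arm". Time is mentioned only for description: proportions, "as well as the infection intensities at each time point, will be summarized and visualized as line-plots over time".
- **Cytokines and antibodies** (Statistical analysis). After log transformation, "linear mixed-effects modeling for analysis will be conducted as outline above".
- **Schedule** (Secondary endpoints). Helminths: "Prevalence and intensity of soil-transmitted helminth infections at 0, 0.5, 3, 6, 6.5, 9, and 12 months". Enteric viruses and bacteria are assessed at 0, 3, 6, 9 and 12 months, cytokines and antibodies at 0, 6 and 12 months.

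No visit, time or treatment-by-visit term is named for any of these models. Nor does the text say that time is left out.

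**The concern.** A covariate set built for one count per child has been carried to outcomes measured three to seven times. With post-baseline data alone the missing visit term would do little harm, because a change common to both arms falls equally on both. The baseline sentence alters that. Since month 0 may not depend on arm, the treatment term can act only after baseline, and its reference level pools both arms' baseline with placebo follow-up. A change shared by both arms then moves albendazole follow-up away from that pooled reference, and part of it is read as a treatment effect.

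Shared change over 12 months is plausible. The children age by a year, and the Study area section describes "two distinct seasons: a rainy season from May to November and a dry season from December to April". That sentence is about climate; the article does not quantify any seasonal or other shared change in these endpoints.

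At stake are the between-arm tests of helminth and enteric infection and of immune response, which supply the trial's evidence on mechanism.

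**Working it through.** **Inputs.** From the article: 700 children randomized 1:1; K post-baseline scheduled visits, with K = 6 (helminths), 4 (enteric pathogens) and 2 (cytokines, antibodies). Assumed, because the article gives no values: within-child correlation ρ from 0 to 0.7, and a shared post-baseline shift δ in SD units with no true treatment effect. The article states no figure for these models, so there is none to reproduce.

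**Model as stated.** y(i,t) = b0 + b1·[albendazole and t > 0] + b2·helminth(i) + u(i) + e(i,t). The condition t > 0 follows from the baseline sentence. Helminth status is balanced between arms by stratification and drops out of the algebra.

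**Share of a sustained shift attributed to treatment.** Solving the generalized least squares equations for a random-intercept model with equal arms gives

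share = 2(1 + Kρ) / (K + 2 + Kρ).

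Example, K = 2 and ρ = 0.5: 2 × 2 / (4 + 1) = 0.80.

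| Endpoint | K | ρ = 0 | ρ = 0.3 | ρ = 0.5 | ρ = 0.7 |
|---|---|---|---|---|---|
| Helminths | 6 | 25% | 57% | 73% | 85% |
| Enteric pathogens | 4 | 33% | 61% | 75% | 86% |
| Cytokines, antibodies | 2 | 50% | 70% | 80% | 89% |

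With a post-baseline (visit) term added, the share is 0 in every cell.

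**False-positive rate.** The variance of b1 is (4/N)(1 − ρ)(1 + Kρ)(K + 1) / [K(K + 2 + Kρ)]. For N = 700, K = 2 and ρ = 0.5 it is (4/700) × 0.30 = 0.00171, so SE = 0.0414.

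- δ = 0.1: bias 0.08, z = 0.08/0.0414 = 1.93, rejection probability about Φ(1.93 − 1.96) = 49%.
- δ = 0.2: bias 0.16, z = 3.86, rejection about 97%.

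Simulation of 1,000 trials per setting agrees (51.5% and 97.4%). Across the three schedules and ρ = 0.3 to 0.7, the simulated rate without visit is 32–83% at δ = 0.1 and 85–100% at δ = 0.2. With the post-baseline term it is 3.8–6.8%, nominal within simulation error.

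**Shift at month 6 only (visits 0, 6, 12).** The two follow-up visits are exchangeable in this model, so each carries half the share: 0.40 at ρ = 0.5. A 0.1 SD shift at month 6 alone gives bias 0.04, z = 0.97 and about 16% false positives; a 0.2 SD shift gives 49%.

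**PBMC cytokines.** Laboratory methods limits these to 20% of children: 0.20 × 700 = 140. Then SE = √(4/140 × 0.30) = 0.0926, and at ρ = 0.5 the rate is about 14% at δ = 0.1 and 41% at δ = 0.2.

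**Logistic models.** The closed form does not carry over exactly. A simulation (700 children, five visits, random-intercept SD 1, prevalence starting at 10% in both arms) gave about 11% false positives when both arms fell to 8%, 59% when both fell to 5% (spurious odds ratio about 0.68), and 43% when both rose to 15% (about 1.23). With visit in the model the rates were close to 5%.

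**The case against.** The strongest reply is that silence is being read as exclusion. A baseline held equal between arms is the usual constrained-baseline longitudinal model, which normally carries visit. The phrase about using the same covariates may mean only the same adjustment set. The document is a journal article, and time coding is often left to a full protocol or SAP that is not shown. This reply stands in part: the authors may well intend a visit term, and a reader who infers that time was deliberately excluded goes beyond the text. It does not remove the point. The covariates are stated by reference, not left open. The baseline sentence forces the treatment term to zero at month 0, but nothing stated adds a main effect of visit. An SAP that followed the stated list would produce a biased test.

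Three stronger readings are tempting and not supported:

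- *All* of a shared change is credited to albendazole. The share is partial and approaches 100% only as the correlation approaches 1.
- All secondary endpoints are affected. The z scores use linear regression adjusted for baseline, adverse events use Fisher's exact test, and microbiota is analysed separately.
- The article documents seasonal enteric exposure. It describes only climate. A purely seasonal change may also have reversed by month 12, in which case the sustained-shift figures are too high.

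**Conclusion.** The point holds as a defect of wording with potentially large consequences, not as proof that the trial's model will be wrong. Followed literally, the stated specification for helminth and enteric infection, cytokines and antibodies does not give a clean between-arm contrast: a sustained shared shift is attributed to albendazole at 57–89% for correlations of 0.3–0.7 and at 25–50% for zero correlation, with half as much if only month 6 of a 0/6/12 schedule shifts. The false-positive figures depend on assumed correlations and shifts and should be read as a range of possibilities, not a forecast. If nothing changes over time in either arm, there is no bias. The primary endpoint is untouched.

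**What to change.** For the repeated-measures infection endpoints, replace the reference to the primary model's covariates with an explicit list: fixed effects of scheduled visit (categorical, including month 0), helminth status at enrollment, and treatment at post-baseline visits (overall or by visit); baseline means constrained equal between arms; random effects as already planned. State that the same specification applies to the cytokine and antibody models.

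The cost is one sentence, two to six visit parameters and no new data. Intervals widen: for visits 0, 6 and 12 at correlation 0.5, the standard error rises from 0.041 to 0.053 SD. The smaller figure is valid only if neither arm changes over time.

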#### Microbiota analyses by 16 s sequencing

DNA extracted from stool samples will be used for high-throughput Illumina sequencing to generate sequence data on the taxonomic composition of the gut microbiota. Sequences will be assigned to operational taxonomic units (OTUs), and the relative abundance of microbial taxa will be calculated using the proportion of OTUs present in each sample. Tests to identify significant differences in the relative abundance of bacterial taxa between groups will be conducted, and *α*-diversity and *β-*diversity measurements will be made. Statistical methods, combining dimension reduction using principal coordinate analysis and regression techniques for correlating microbiota analysis and parasite identification with immune data from blood, will be used to generate a comprehensive portrait of cellular and molecular events in the intestinal tract.

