### Sample size and statistical considerations

In southern Vietnam, approximately 30 % of school-aged children are infected with at least one species of STH [20]. This percentage was supported by our preliminary study of helminth infections in healthy children in Ho Chi Minh City, Vietnam (our unpublished data). Most data on diarrheal incidences due to enteric infections have focused on children under 5 years of age. For the bacterial pathogens, *Shigella*, *Campylobacter*, and *Escherichia coli*, diarrheal rates in this age group range from 3.3 cases/child per year in children under 1 year old to 0.7 cases/child per year in 4-year-olds in Vietnam [36]. Few studies have investigated the incidence of diarrheal events in children over 5 years of age. Considering the diarrheal attack rate in 4-year-olds due to these three pathogens, it is estimated that school children over 5 years of age will have a probability of at least 0.6 of experiencing one or more diarrheal episodes due to any viral or bacterial species during the 12-month follow-up duration. The clinical trial is powered to detect a 15 % absolute increase of this probability (from 0.6 to 0.75) due to anthelmintic treatment in both the subgroups of helminth-infected and helminth-uninfected participants. For 80 % power at the two-sided 5 % significance level, a total of 298 helminth-infected and 298 helminth-uninfected participants will be needed. Of note, this sample size calculation is conservative insofar that the actual study endpoint measures the number of diarrheal episodes and is thus more sensitive than the binary assessment of whether at least one episode occurred or not. To account for potential inadequacies in our assumptions and some loss to follow-up, the sample size was increased by 15 %. Thus, a total sample size of 700 participants: 350 helminth-infected and 350 helminth-uninfected children, will be recruited from the baseline study (using a random number generator to subsample from those groups, as needed) to the clinical trial and will be equally randomized to receive either anthelmintic or placebo treatment. Assuming that approximately 30 % of school-aged children are infected with at least one species of STH infection [20], to enroll 350 helminth-infected children, up to 1800 school children will be enrolled in the baseline study, in order to account for any uncertainties in the helminth prevalence during the baseline study and for decreased participant enrollment for the clinical trial.

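### Taxon-by-taxon significance tests are planned across several contrasts with no stated control of false discoveries

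*Protocol article*

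**What the plan says.** Testing at the level of single taxa is announced twice. Under Microbiota analyses by 16 s sequencing: "Tests to identify significant differences in the relative abundance of bacterial taxa between groups will be conducted". Under Statistical analysis, tests of this kind "will be used to identify significant differences in bacterial taxa between the different groups of interest". LEfSe is the only test named, and it is named as an example.

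Statistical analysis also sets out the comparisons. Composition is examined before and after helminth infection, treatment and diarrhea, and it "will be compared with individual baseline levels, between the two treatment arms, and between helminth-infected and helminth-uninfected individuals". The same section adds: "Subgroup analyses according to helminth infection status at enrollment (infected versus uninfected) will also be performed for all endpoints". Secondary endpoints lists six scheduled microbiota time points (0, 0.5, 3, 6, 9 and 12 months), plus samples during and after diarrhea.

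One correction is mentioned, in the sentence on the mothur pipeline. It is there "to apply appropriate corrections for any differences driven by rare taxonomic groups of microbes". The article gives no significance level for the taxon tests, no number of taxa, and no false-discovery or family-wise control.

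**The concern.** The text commits to calling taxa significant and goes as far as naming a tool and a correction, but neither limits false discoveries. LEfSe applies a rank test to each taxon at a fixed level and then keeps those with a large enough effect score. The score filter removes small differences; it is not an error-rate control. The rare-taxa correction addresses differences driven by sparse groups, not the number of taxa tested.

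The stake is interpretive. Study aims gives the gut microbiota as one of two routes by which deworming might raise diarrheal incidence, and the Discussion hopes that these samples will point to mechanisms. Taxa that differ between arms by chance could be read as support for such a mechanism. Statistical analysis uses the word exploratory for analyses that add the extra stool samples linked to diarrhea, but it does not apply that label to the taxon results.

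**Working it through.** The plan states no figure on this point, so there is none to reproduce.

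**Inputs**
- Contrasts: at least 3 (own baseline, arms, infection status), from Statistical analysis.
- Per-taxon level α: not stated. The 5% level in Sample size and statistical considerations ("For 80 % power at the two-sided 5 % significance level") belongs to the sample size, so α = 0.05 is an assumption here. Levels of 0.01 and 0.001 are also shown.
- Number of null taxa M: not stated; 20 to 200 assumed.
- All figures are before the LEfSe effect-size filter, whose effect cannot be calculated from the article.

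**Step 1. One contrast, independent null taxa**

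Expected false taxa = α × M. Chance of at least one = 1 − (1 − α)^M. With α = 0.05:

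| M | Expected false taxa | Chance of at least one |
|---|---|---|
| 20 | 0.05 × 20 = 1 | 1 − 0.95^20 = 0.64 |
| 50 | 0.05 × 50 = 2.5 | 1 − 0.95^50 = 0.92 |
| 100 | 0.05 × 100 = 5 | 1 − 0.95^100 = 0.994 |
| 200 | 0.05 × 200 = 10 | above 0.999 |

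**Step 2. Three contrasts, treated as independent**

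For 20 taxa, 60 tests give 3 expected false taxa and a chance of 1 − 0.95^60 = 0.95 of at least one. For 100 taxa, the expected number is 15.

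**Step 3. Correlated taxa**

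Equicorrelated normal statistics, 100 null taxa, two-sided 5%, 4,000 simulations:

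| Correlation | Chance of at least one | Mean number false |
|---|---|---|
| 0.3 | 0.94 | 4.9 |
| 0.6 | 0.65 | 5.2 |
| 0.9 | 0.23 | 5.0 |

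Correlation lowers the chance of any false taxon. It leaves the expected number at about 5, because false calls then arrive in clusters.

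**Step 4. Stricter level**

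For 100 independent null taxa in one contrast, α = 0.01 gives 1 expected and a chance of 0.63; α = 0.001 gives 0.1 expected and 0.10.

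**Step 5. With Benjamini-Hochberg at 5%**

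All taxa null and independent, 20,000 simulations: the chance of any false taxon in one contrast is about 0.052 for 50, 100 or 200 taxa, which is 0.05 within simulation error. Over three independent contrasts, each controlled at 5%, it is 1 − 0.95^3 = 0.14.

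**The case against.** The strongest reply is that this is a condensed article, that p-value adjustment for a secondary sequencing analysis is commonly left to the analysis plan, and that nothing in the text forbids it. The words introducing LEfSe make it an example, so neither the method nor its threshold is fixed. This stands in part: silence on adjustment would not by itself be a finding. What remains is that the section does address both tool and correction, and the only ones it names leave the number of taxa tested unaddressed.

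A reader might infer that the plan tests every taxon at 5% and that false taxon findings are therefore close to certain. The documents do not support that. They give no level and no number of taxa. Independence cannot hold exactly, since the data are proportions within each sample. The effect-size filter would act after the counts shown above. Strong correlation or a strict level brings the chance of any false call well down. Nor does the article say that the taxon tests are repeated at every visit; it lists sampling times only.

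It is also fair that adjusting within each contrast leaves some error across contrasts (0.14 in the last step above), and that labelling the results exploratory would meet much of the concern. Both points are accepted.

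**Conclusion.** The point holds as a modest one. Significance is to be declared taxon by taxon over several contrasts, and neither the example test nor the stated correction controls false discoveries. At an assumed 5% level, about 5 false taxa per contrast are expected from 100 null taxa, whatever their correlation, and 1 from 20. The chance of at least one depends on the assumptions: from 0.23 to 0.994 for 100 taxa as correlation falls from 0.9 to zero. All of these precede the effect-size filter.

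The endpoint is secondary and mechanistic, and the primary comparison of diarrheal episodes does not rest on it. A reader might go further and conclude that the plan will report taxa as changed by albendazole when none is. That would require a level, a taxon count and a dependence structure that the article does not give.

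**What to change.** In the microbiota paragraph of Statistical analysis, add that:

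- whichever taxon-level test is used, its p values are adjusted by Benjamini-Hochberg at a 5% false discovery rate across the taxa, and across any visits tested, within each contrast;
- only taxa that pass are called significant;
- the LEfSe effect score is used to rank taxa, not to declare them;
- any taxon results reported without adjustment are labelled exploratory.

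The cost is a few lines of text and one line of code, and fewer taxa will be reported as significant. No data collection changes, and the primary endpoint is unaffected. Label: cheap improvement.
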